**Conclusions:**

The results of this study will further elucidate the role of affect in glucose variability. By identifying affective states that may lead to glucose excursions, our findings could inform just-in-time behavioral interventions by indicating opportunities for intervention delivery.

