## Methods

This is a 14-day observational study. Enrolled participants (N=100) will wear a CGM and receive EMA prompts to assess affect 6 times per day over the 14-day period (detailed below).

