#### Glucose Monitoring

Participants will wear a FreeStyle Libre Pro CGM sensor (Abbott) on the upper arm of the participant’s choosing for 14 days. The FreeStyle Libre Pro collects blinded interstitial glucose levels at 15-minute increments.

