#### Affect

During the 14-day data collection period, participants will receive EMA prompts delivered to their smartphone via the Ethica mobile app (Ethica Data). Prompts will be delivered 6 times per day. One prompt will be delivered at a random time within each 2-hour window between 8 AM and 8 PM (8 AM-10 AM, 10 AM-12 PM, 12 PM-2 PM, 2 PM-4 PM, 4 PM-6 PM, and 6 PM-8 PM). Each prompt will consist of 10 Likert-scale items that will assess both positive and negative affect, with responses ranging from 1 (not at all) to 4 (extremely): “How (happy, cheerful, relaxed, stressed, anxious, angry, sad, energetic, tired, lonely) do you feel?” The survey will also include 2 “yes” or “no” questions: “Are you (bored, hungry) right now?”

The order of the 10 items will be randomized at each time point. Assessment questions have been validated for their use in daily or momentary assessment [30-32].

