### Analysis

We will determine compliance to CGM and Fitbit wear (% of wear time) and response rates to EMA prompts (% of prompts responded to). Predetermined compliance values (CGM and Fitbit wear ≥80%) and EMA response rates (75%) will be used to assess the feasibility of the study procedures.

Multilevel linear regression models, which adjust the standard errors for the clustering of EMA and glucose data within individuals and partition the variance of between- and within-person effects, will be used to evaluate the acute relationship between glucose level and affect. The following two outcome variables will be evaluated: (1) average glucose level in the time period between 2 EMA prompts and (2) occurrence of a glucose excursion (defined as a glucose level greater than 1 SD above the mean 24-hour glucose level). Predictor variables will be 2 separate composite scores for positive affect (average of “happy,” “cheerful,” “relaxed,” and “energetic”) and negative affect (average of “stressed,” “anxious,” “angry,” “sad,” and “tired”). Secondary analyses will be used to predict the interaction effects of physical activity, sleep, and affect on glucose level. Similar models will evaluate positive and negative affect as the outcome variable and average glucose level in the hour prior as the predictor. Covariates in the model will include age, sex, BMI, time of day, day of week, physical activity since the previous EMA prompt, and previous night’s sleep. Additional baseline measures will be evaluated as potential covariates and included in the final model if found to significantly improve model fit. Instances of missing EMA or CGM data will be excluded from the analysis.

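### The excursion outcome is defined by glucose level alone and no model term accounts for glucose at the rating, so excursions already under way can be credited to affect

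*Protocol article*

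**What the plan says.** The Analysis section names two glucose outcomes. The first is "average glucose level in the time period between 2 EMA prompts". The second is "occurrence of a glucose excursion (defined as a glucose level greater than 1 SD above the mean 24-hour glucose level". The second carries no window of its own, and it does not ask for an upward crossing, a start after the rating, a minimum duration or a return below the cut-off.

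On adjustment the same section says "Covariates in the model will include age, sex, BMI, time of day, day of week, physical activity since the previous EMA prompt", and then adds the previous night's sleep. Other baseline measures may enter if they improve fit. Nothing in the list describes glucose at or before the rating.

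The reverse direction is analysed as well: "Similar models will evaluate positive and negative affect as the outcome variable and average glucose level in the hour prior as the predictor". The Discussion hypothesises both paths, with negative affect raising glucose variability and glucose variability raising negative affect. The abstract's Conclusions read the excursion result in one direction: "By identifying affective states that may lead to glucose excursions", with just-in-time interventions as the use.

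The schedule is given under Affect: "One prompt will be delivered at a random time within each 2-hour window between 8 AM and 8 PM". Under Glucose Monitoring: "The FreeStyle Libre Pro collects blinded interstitial glucose levels at 15-minute increments".

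**The concern.** The stated use of the excursion model is to find affective states that come before an excursion, so that an intervention can be delivered in time. An outcome defined by level does not separate an excursion that starts after the rating from one that started earlier and has not yet ended. The second kind cannot have been led to by that rating.

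Two errors follow, depending on whether glucose really moves mood:

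- **If it does**, as the study hypothesises, high glucose before the prompt raises negative affect, stays high past the prompt, and is scored as an excursion that negative affect predicted. The false association has the same sign as the hypothesised one, and the two directions the study wants to tell apart are mixed.
- **If it does not**, the carried-over events are unrelated to the rating and dilute any true effect.

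Where windows adjoin, an excursion that spans a prompt is also counted in both intervals.

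**Working it through.** The article gives no excursion rate, duration or effect size, so there is no stated figure to reproduce. The checks below use the schedule plus labelled assumptions.

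**Inputs from the article.** "Enrolled participants (N=100) will wear a CGM and receive EMA prompts to assess affect 6 times per day over the 14-day period". Six adjoining 2-hour windows give 5 within-day intervals, so at most 100 × 14 × 5 = 7,000. The gap between prompts is 120 + U₂ − U₁ minutes, with each U uniform on 0 to 120, so it averages 120 and ranges from 0 to 240. At 15-minute sampling an average interval holds 120/15 = 8 readings.

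**Assumptions.** Excursion duration D of 30, 60, 90 or 120 minutes. Share of time above the cut-off p = P(Z > 1) = 15.9% if readings are normal (0.159 × 24 = 3.8 hours a day), with 25% as a daytime alternative. Waiting time from the end of one excursion to the next onset is exponential. The outcome is positive if glucose is above the cut-off at any time in the between-prompt interval.

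**Step 1: counting in more than one interval.** Away from the ends of the day, prompts have density 1 per 120 minutes. An excursion therefore spans D/120 prompts on average and touches 1 + D/120 intervals: 1.25, 1.50, 1.75 and 2.00 for the four durations. By simulation of the schedule, with starts uniform from 10 AM to 4 PM, the chance of spanning at least one prompt is 25%, 48%, 68% and 84%.

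**Step 2: positive intervals already above the cut-off at the opening prompt.** The onset rate while below the cut-off is λ = p/[D(1 − p)]. With x = 120λ, averaging over the gap gives P(no onset | below) = [(1 − e^(−x))/x]², so

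P(positive) = 1 − (1 − p)·[(1 − e^(−x))/x]², and the share opening above = p / P(positive).

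For D = 60 and p = 0.159: x = 120 × 0.159/(60 × 0.841) = 0.377; the squared term is 0.694; P(positive) = 1 − 0.841 × 0.694 = 0.416; share = 0.159/0.416 = 38%.

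| D (min) | P(positive), p = 15.9% | Opening above | No new onset (simulated) | P(positive), p = 25% | Opening above | No new onset (simulated) |
|---|---|---|---|---|---|---|
| 30 | 0.585 | 27% | 15% | 0.771 | 32% | 12% |
| 60 | 0.416 | 38% | 29% | 0.600 | 42% | 26% |
| 90 | 0.342 | 46% | 39% | 0.511 | 49% | 37% |
| 120 | 0.301 | 53% | 48% | 0.458 | 55% | 46% |

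Simulation of the same set-up agrees with the formula to within about one percentage point. The no-new-onset share is smaller because some intervals that open high also contain a later, separate onset.

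**Step 3: a different model of the day.** This used 3 meals and up to 2 snacks, a mean post-meal rise of 35 mg/dL peaking at 30, 45 or 60 minutes, and autocorrelated noise. It flagged 0.51, 0.51 and 0.49 of intervals, and 33%, 39% and 42% of those opened above the cut-off. The share of all intervals opening above is then 0.51 × 0.33 = 17% up to 0.49 × 0.42 = 21%.

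**Step 4: effect on the inference.** Suppose affect is 0.3 SD higher when glucose is already high and has no effect on onset. With 7,000 intervals, p = 15.9%, ordinary logistic regression and 15 runs per duration:

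| D (min) | Odds ratio, any time above cut-off | Runs rejecting | Odds ratio, onset in intervals opening below | Runs rejecting |
|---|---|---|---|---|
| 30 | 1.07 | 73% | 0.99 | 1 of 15 |
| 60 | 1.12 | 100% | 1.00 | 0 of 15 |
| 90 | 1.14 | 100% | 0.99 | 1 of 15 |

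**Step 5: dilution without a reverse path.** An interval that opens above the cut-off is positive whatever the rating, so its slope on affect is zero. In a linear model the pooled slope is (1 − p) times the slope among intervals opening below: 0.84 of it at p = 15.9% and 0.75 at p = 25%.

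**The case against.** The strongest reply is that the article does not contain the rule being criticised. The between-prompt window belongs to outcome 1. Outcome 2 has neither a window nor a counting rule, and a condensed article may leave such detail to a fuller document. This stands in part. A reader might infer that the plan states an any-reading rule over adjoining intervals and so certainly double counts; the text does not say that. Scoring over outcome 1's period is the natural reading, not a quoted rule, and the double count also needs windows that adjoin. What the article does fix is a definition by level and a covariate list without glucose state, and these produce the ordering problem for any window that opens at the rating.

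A second tempting reading is that only a redefined outcome can help and no covariate would. That is wrong for the affect coefficient. Every interval opening above the cut-off is positive by construction, so in a logistic model an indicator for that state predicts those intervals perfectly and they contribute nothing further. In a check with 60-minute excursions (p = 15.9%, 8 runs), the coefficient was 0.105 unadjusted, −0.012 with the indicator and −0.012 with those intervals excluded; with a true effect it was 0.216 both ways. A linear model with the indicator also removed the false effect (−0.002), although by Step 5 it would still shrink a true one. A continuous earlier-glucose covariate was not tested.

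Third, the aims are wider than onset: the article speaks of an acute, bidirectional relationship and hedges its conclusion. So the level-based outcome still has descriptive value. It does not support the reading that affect leads to excursions.

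Finally, the percentages are soft. That is accepted; they are given as ranges.

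**Conclusion.** The point holds as a fault in how outcome 2 is fixed for its stated purpose. The definition and the listed covariates let excursions in progress at the rating count as events that affect predicted, and the study's own reverse hypothesis turns this into a possible false association rather than mere noise.

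Over the assumed durations (30 to 120 minutes) and prevalences (15.9% and 25%), about 27% to 55% of positive intervals would open above the cut-off and 12% to 48% would hold no new onset. The false odds ratios of 1.07 to 1.14 depend further on the assumed 0.3 SD effect and on an ordinary rather than multilevel model. They show that the mechanism works and do not predict this study's result.

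The documents do not support saying that any association found will be spurious. Nor does an onset after the rating prove that affect came first: a meal eaten before the prompt can push glucose over the cut-off after it.

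**What to change.** 1. State the window for outcome 2 and have it start at the affect rating.
2. In the primary excursion model, include only intervals whose last CGM reading at or before the rating is at or below the cut-off. Score the first upward crossing after the rating, once per interval. Later intervals become eligible again when they open at or below the cut-off.
3. Alternatively, keep all intervals in a logistic model with an indicator for being above the cut-off at the rating. The affect coefficient is the same, but perfect prediction can stop the fit converging, so exclusion is simpler. In a linear model the two are not equivalent.
4. Add a simple rule, such as a minimum run of readings below the cut-off, so that noise around it is not counted as a new onset.
5. Report the unrestricted level-based version as a sensitivity analysis.
6. Say in the interpretation that this removes excursions already under way but does not place affect before the meal behind the rise.

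The cost is a few sentences and a few lines of code; the 15-minute readings are already collected. Intervals opening above the cut-off leave this one model: about 17% to 21% under the assumed meal shape, or 16% to 25% under the assumed prevalences, with the corresponding loss of precision.

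### The stated covariates adjust for time of day and day of week but not for study day, so a drift common to affect and glucose over the 14 days would enter the within-person slope

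*Protocol article*

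**What the plan says.** The Analysis section uses multilevel linear models that "partition the variance of between- and within-person effects, will be used to evaluate the acute relationship between glucose level and affect". For the reverse direction it says: "Similar models will evaluate positive and negative affect as the outcome variable and average glucose level in the hour prior as the predictor". One covariate list follows: "Covariates in the model will include age, sex, BMI, time of day, day of week, physical activity since the previous EMA prompt", together with the previous night's sleep. The list is extended by one rule: "Additional baseline measures will be evaluated as potential covariates and included in the final model if found to significantly improve model fit".

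On the data, Methods says: "Enrolled participants (N=100) will wear a CGM and receive EMA prompts to assess affect 6 times per day over the 14-day period". The Affect section repeats the rate ("Prompts will be delivered 6 times per day") and gives the same ten rating items at each prompt. Under Glucose Monitoring, the sensor is worn "on the upper arm of the participant’s choosing for 14 days".

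No term for study day, elapsed wear or trend appears in the article. The only other change over the period that it considers is in weight, measured once at the follow-up visit and only possibly used in analysis.

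**The concern.** The question of interest is whether glucose moves with affect, from moment to moment, within a person. Two series that both trend over the same 14 days are correlated within that person even when neither influences the other. Person-level random effects or person-mean centring remove stable differences between people, but not a trend inside a person. Time of day and day of week are cyclic and do not represent it, and a baseline measure is constant within a person.

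Possible sources of trend are habituation to up to 84 near-identical prompts, gradual change in the sensor reading, and changed habits while being monitored. Drift in the same direction in both series pushes the slope upward, and drift in opposite directions pushes it downward. A common trend could therefore create an association or hide a small real one. Because the models run in both directions, one trend could produce two apparent associations, which would resemble the bidirectional relationship hypothesised in the Discussion.

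**Working it through.** The article gives no power, alpha or drift figure, so there is nothing of its own to reproduce. The drift sizes below are assumptions.

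**Records.** Inputs are 100 participants, 14 days, 6 prompts a day and the 75% response figure, which the article offers only as a feasibility threshold ("EMA response rates (75%) will be used to assess the feasibility of the study procedures").
- All answered prompts: 100 × 14 × 6 × 0.75 = 6,300. This suits the reverse model.
- The forward outcome is mean glucose between two prompts, and six prompts give five daytime intervals. With one answered prompt needed per interval: 100 × 14 × 5 × 0.75 = 5,250.
- With both bounding prompts needed: 100 × 14 × 5 × 0.75² ≈ 3,938.

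**Does day of week stand in for study day?** The variance of 14 consecutive days is (14² − 1)/12 = 16.25. Each weekday occurs twice, 7 days apart, so the variance of day within a weekday is 3.5² = 12.25. If everyone started on the same weekday, 12.25/16.25 = 75% of the study-day variance would remain. With mixed start days nearly all remains.

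**Spurious slope.** A linear drift of d within-person SD from day 1 to day 14 has variance d² × 16.25/13² = 0.0962 d². With no true effect, the slope of glucose on affect is 0.0962 × d_A × d_G / (1 + 0.0962 × d_A²). At d = 0.5 in both series this is 0.02405/1.02405 = 0.0235. The correlation of each series with day is then √0.0235 ≈ 0.15.

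**Simulation.** The set-up was 100 people, 14 days, 6 prompts and 75% answered (about 6,300 records), with independent residuals, mixed start days and no true effect. The model was person-mean-centred with day-of-week and time-of-day terms, tested two-sided at 5%, with 400 replicates per setting.

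| Drift in each series (SD) | Formula slope | Simulated slope, no study day | Rejection, no study day | Rejection, linear study day added |
|---|---|---|---|---|
| 0 | 0 | 0.001 | 6% | 4% |
| 0.2 | 0.004 | 0.004 | 5% | 6% |
| 0.3 | 0.009 | 0.009 | 9% | 5% |
| 0.5 | 0.0235 | 0.023 | 44% | 5% |
| 0.8 | 0.058 | 0.059 | nearly 100% | 5% |

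With 0.5 SD drift in affect and none in glucose, the slope was about 0 and rejection 3%. Drift in one series alone gives no bias. If everyone starts on the same weekday, the 0.5 SD case falls to a slope of 0.019 and 34% rejection.

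**Sensitivity to the number of records.** Let both series correlate with day at r_day. The spurious correlation is r_day², z = r_day² × √n, and the rejection probability is P(|Z + z| > 1.96).
- r_day = 0.05, n = 6,300: correlation 0.0025, z = 0.20, rejection 5.5%.
- r_day = 0.10, n = 6,300: correlation 0.010, z = 0.79, rejection 12.5%.
- r_day = 0.15: correlation 0.0225. At n = 6,300, z = 1.79 and rejection is 43%. At n = 5,250, z = 1.63 and 37%. At n = 3,938, z = 1.41 and 29%.
- r_day = 0.20: correlation 0.040. Rejection is 89%, 83% and 71% at the same three sizes.

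Solving r_day² = 0.0962 d²/(1 + 0.0962 d²) for d, the values 0.15 and 0.20 correspond to drifts of about 0.49 and 0.66 SD over the 14 days, in both series.

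**The case against.** The strongest objection is that the harm rests on a premise the article does not document. Bias needs drift in both series, with a consistent sign across participants. Person-specific drifts without a common direction average out, and no section reports drift in either series. This stands, and it makes the point conditional.

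The design also weakens some routes to drift. Glucose readings are hidden from participants, so they cannot react to them. Change prompted by the activity tracker would run largely through activity and sleep, which are already covariates. This also stands, but it leaves prompt habituation, sensor drift and dietary change open.

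A reader might infer that, with thousands of records, even a weak shared trend produces a false positive. The figures do not support that: rejection is 5% at 0.2 SD and about 9% at 0.3 SD. Even at 0.5 SD the spurious correlation explains only about 0.05% of variance (0.0225² ≈ 0.0005), so it could mask only a similarly small true effect.

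The excursion outcome is defined against a 24-hour mean. If that mean is computed for each day, slow drift in level is largely removed from it. The text does not settle this, so the concern should not be extended to that outcome with equal force.

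Finally, the article is condensed and does not call its covariate list exhaustive, so a fuller plan might contain a trend term. That is fair. But the article does state both a list and a rule for extending it, and neither leads to study day.

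**Conclusion.** The point holds as a minor, conditional one. The stated covariates and the stated rule for adding to them leave a within-person linear trend unadjusted in both model directions. If affect and glucose each drift by about 0.5 within-person SD over the 14 days, in a consistent direction across participants, the false-positive rate is roughly 29% to 43% for about 3,900 to 6,300 records. Below about 0.3 SD the effect is negligible.

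These figures assume linear drift, independent residuals, 75% response and no CGM loss. The documents neither show nor exclude drift of any size. They therefore do not support a claim that the planned analysis will give a false answer, only that it has no stated protection against this one.

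**What to change.** Add study day (1 to 14, linear) as a covariate in the forward and reverse models, and specify it before analysis so that it is not a post hoc choice. The cost is one degree of freedom per model. Study day is known for every record, so no new data or change of procedure is needed. A separate day-1 indicator is optional: the linear term alone restored the nominal error rate under the linear drifts simulated. It would also help to state whether the 24-hour mean in the excursion definition is computed per day, since that decides how far that outcome is exposed.

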## Results

Recruitment started in October 2022. As of December 12, 2022, a total of 39 participants have been enrolled. We expect to enroll 100 participants by a target completion date of March 2023.

## Discussion

This project will generate data to elucidate the relationship between affective states and glucose variability, with an aim of ultimately informing intervention development to reduce glucose variability. We hypothesize that a bidirectional relationship exists by which greater negative affect will predict greater glucose variability, while greater glucose variability will predict greater negative affect.

Technological innovations hold promise for improving approaches to understand the relationship between affective states and glucose variability in real-world settings. CGMs allow for real-time collection of data related to postprandial response, while EMA allows for real-time collection of mood states. Pairing these approaches will facilitate a more valid evaluation of the relationships between affective states and eating behavior, as well as provide opportunities for real-time precision nutrition interventions that consider individuals’ physiological and cognitive states. Precision intervention approaches, such as just-in-time interventions, aim to intervene during moments of opportunity [6]. Compliance data, along with the postparticipation questionnaire, will inform changes to study procedures to address the barriers experienced by participants. Evaluation of the relationship between glucose level and affect will aim to identify situations in which glucose excursions occur (opportunity) and can inform interventions to be delivered during those opportunities (ie, meditation or physical activity to improve affect and dietary suggestions that minimize glucose excursions).

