## Introduction

Effective intervention strategies are required to reduce the immense burden of cardiometabolic disease. Standard behavioral interventions to reduce cardiometabolic disease risk are typically based on population averages [1,2]; however, variability in response to dietary interventions suggests the need for personalized approaches [3]. Precision approaches aim to tailor interventions to an individual’s unique characteristics and contexts [4,5]. For example, just-in-time adaptive interventions aim to facilitate behavior change by delivering an intervention at times and in contexts when individuals are more receptive to behavior change [6]. Identifying opportunities for change requires an understanding of the time-varying factors that influence behaviors.

The potential to measure time-varying factors has increased with the availability of wearable sensors. The use of continuous glucose monitors (CGMs) has resulted in the identification of glucose variability, that is, intraday fluctuations in blood glucose, as a risk factor for the development of cardiometabolic disease [7]. Greater glucose variability predicts increases in glycated hemoglobin (HbA_1c_) in both diabetic and nondiabetic populations [8,9]. Among persons with type 2 diabetes who maintain good glycemic control (HbA_1c_≤7.0%), greater glucose variability was an independent risk factor for coronary artery disease during a 10-year follow-up period [10]. Though evidence in nondiabetic populations is sparse, mechanistically, it has been proposed that glucose variability increases cardiovascular disease risk through increased oxidative stress and inflammation [11], an effect that has been observed among individuals with normal insulin function [12].

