While several factors influence glucose levels (eg, stress, physical activity, etc), glucose variability is primarily driven by increases in postprandial glucose [13]. Controlled laboratory studies have demonstrated that several dietary factors impact postprandial glucose, such as meal composition [14,15], meal timing [16], and meal frequency [17]. In real-world settings, eating behavior, and thus glucose variability, is influenced by several individual-level factors. One example of an individual factor that influences eating behavior is affect [18-21]. The relationship between eating behavior and affect appears to be bidirectional as fatigue, stress, and negative mood are associated with increased cravings and food consumption [19-22], while variations in glucose in response to eating may relate to affective and physical feeling states [23-26]. However, research in this area has primarily relied on dietary assessment recall methodologies, which may be prone to bias and recall error [27]. Pairing data from CGMs with data on affect using ecological momentary assessment (EMA), which involves repeated sampling of affect in real time and in an individual’s natural environment, improves the validity of responses [28] and dramatically decreases the time between measurement of mood and glucose.

Combining CGM and EMA data to investigate the relationship between affective states and glucose variability presents an opportunity to support the development of precision interventions to prevent chronic disease by identifying situations that are likely to lead to large glucose increases (ie, an opportunity for change). A recent review [29] of mood and glucose variability in type 1 and 2 diabetes identified only 1 study that used CGMs and EMA to evaluate mood and glucose [25] and called for more research evaluating the relationships between mood or affect and glucose variability. To date, only a small (n=15) pilot study has combined EMA responses with CGM data to evaluate its association with affective and physical feeling states in nondiabetic samples [18]. Thus, the aims of this study are to (1) evaluate the feasibility of conducting a study using CGMs and EMA and (2) examine the bidirectional relationship between affect and glucose in adults using CGM and EMA data.

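### The hypothesis is about glucose variability, but no direct variability measure is planned: glucose-to-affect is untested, and affect-to-glucose rests on a binary excursion proxy

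*Protocol article*

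**What the plan says.** All references are to the protocol article.

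- **Definition.** The Introduction describes "glucose variability, that is, intraday fluctuations in blood glucose".
- **Hypothesis.** The Discussion states the only explicit hypothesis, and states it in both directions: "greater negative affect will predict greater glucose variability, while greater glucose variability will predict greater negative affect".
- **Affect predicting glucose (forward).** The Analysis section names two outcomes. The first is "average glucose level in the time period between 2 EMA prompts". The second is "2) occurrence of a glucose excursion (defined as a glucose level greater than 1 SD above the mean 24-hour glucose level".
- **Glucose predicting affect (reverse).** "Similar models will evaluate positive and negative affect as the outcome variable and average glucose level in the hour prior as the predictor".
- **Formal aim.** The second aim in the Introduction is to "examine the bidirectional relationship between affect and glucose in adults using CGM and EMA data". It does not mention variability.
- **Conclusions.** The Abstract expects the results to clarify how affect bears on glucose variability, and then refers to affective states that precede excursions.

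**The concern.** The hypothesis is about fluctuation, while most of the named glucose variables are levels. The Analysis section does not leave the choice open: it lists two outcomes and names the reverse predictor. This is therefore a mismatch between stated items, not a detail that an article would leave to a fuller document.

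There are two risks. A positive or null result on mean glucose could be reported as evidence on variability, which it is not. And if a variability index is chosen only after the data have been seen, the test of the study's one stated hypothesis is no longer prespecified.

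**Working it through.** The plan gives no figure to reproduce here. The check compares each half of the hypothesis with the variable assigned to it.

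**Reverse: variability predicting negative affect.**
The Glucose Monitoring section gives one reading every 15 minutes, so the preceding hour holds about 60/15 = 4 readings. Take two illustrative hours (mg/dL):
- 100, 100, 100, 100: mean 100, SD 0.
- 70, 130, 75, 125: mean 400/4 = 100. Squared deviations are 900 + 900 + 625 + 625 = 3050, so SD = √(3050/3) = 31.9.

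The planned predictor gives both hours the same value. In a simulation on assumed values (described below, SD 16), the correlation between the mean and the SD within an hour was −0.003. Nothing else in the reverse model carries spread.

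**Forward, first outcome: mean glucose between prompts.**
The eight readings 90, 105, 130, 140, 125, 100, 80, 78 have mean 848/8 = 106 and SD √(3846/7) = 23.4. A flat window at 106 has the same mean and SD 0. This outcome cannot tell them apart.

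**Forward, second outcome: the excursion.**
This one can tell the same two windows apart. Assume a 24-hour mean of 100 (not in the documents). The first window peaks at 140 and is flagged if 140 > 100 + SD, that is, for SD below 40. The flat window is flagged only if 106 > 100 + SD, that is, for SD below 6. For any SD from 6 up to 40 the outcome separates them.

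How far it measures variability depends on whose SD is meant. Write a reading as x = m + s·z, with m and s the day's mean and SD. If the threshold is m + s, the condition reduces to z > 1 and s drops out. If the threshold is m + c, with c fixed across days, the condition is z > c/s, which is met more often as s grows.

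The simulation used 4000 days of 96 readings, lag-1 correlation 0.9, mean 100, and six 2-hour windows from 8 AM to 8 PM. All values are assumptions. Share of windows with at least one excursion:

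| True SD | Threshold uses day's own SD | Threshold uses common SD of 16 |
|---|---|---|
| 8 | 41% | 5% |
| 16 | 42% | 34% |
| 24 | 41% | 50% |

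Under the first reading the indicator marks when highs occur within a day, but is normalised for how variable that day is. Under the second it tracks variability. Under both it is one-sided: a sustained high counts and a fall below the mean does not.

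**The case against.** The strongest reply is that the forward direction does contain a variability outcome. An excursion is an upward fluctuation within the day. The Introduction says variability is driven mainly by postprandial rises, and the Abstract and Discussion treat excursions as the target for intervention. Even with a day's-own SD, the indicator shows which windows of the day contain a rise, and that is close to what a momentary model of affect asks. This stands. A reader might infer that no planned variable reflects variability, or that the excursion carries none because it is scaled by the SD. The documents do not support either: the excursion is a planned proxy, and the scaling argument holds only for the day's-own SD, which the Analysis section does not specify.

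A second reply is that the formal aims speak of affect and glucose without mentioning variability, so the planned models meet them. This also stands. It limits the consequence but does not remove the mismatch with the stated hypothesis or with the first sentence of the Abstract's conclusions.

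A third is that a fuller plan may hold a variability index. That would not resolve the point, because the article names its outcomes and its reverse predictor outright.

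No reply rescues the reverse direction.

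**Conclusion.** The point holds in a bounded form. No direct variability index is planned. The reverse half of the hypothesis is not tested, because its only glucose term is a mean; this needs no assumption beyond the text. The forward half is addressed only through a coarse, binary, one-sided proxy. Its relation to variability ranges from none between days (about 41% of windows flagged at every SD) to strong (5% to 50%), according to an SD that is not identified. Those percentages rest on the simulation's assumed values; the algebra behind them does not.

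It would go too far to say that the hypothesis can be neither supported nor refuted in either direction, or that the conclusions would rest on glucose level alone. The excursion model bears on the forward half, and the formal aims can be answered as planned.

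**What to change.** Choose one of two routes before the analysis begins.

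1. **Add a variability index.** From the existing CGM readings, prespecify a within-window SD or CV.
   - Forward: use it as an outcome over a stated window after the prompt, with a minimum number of readings.
   - Reverse: use it as a predictor over a stated window before the prompt, with mean glucose over that window in the same model.
   - Keep the mean-glucose and excursion models, and say whether the excursion SD is that of the day, the person or the whole sample.
2. **Restate the claim.** Word the hypothesis and conclusions as concerning glucose level and excursions.

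The window length needs care. The interval between prompts is a poor choice for the forward index. With one prompt uniformly timed in each 2-hour block, the gap between consecutive prompts runs from near 0 to 4 hours, and (1 × 1/2)/(2 × 2) = 1/8 of gaps are under 1 hour. For roughly normal, independent readings the relative standard error of an SD is about 1/√(2(n − 1)): 41% for 4 readings (1 hour) and 27% for 8 (2 hours). Autocorrelated readings carry less information than this assumes. A 2-hour window is therefore more defensible than 1 hour, though still noisy.

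The first route costs some extra analysis and imprecise indices in short windows. The second costs only wording. Neither needs new data.
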